## Abstract

**Background:**

Major depressive disorder (MDD) imposes a heavy global disease burden. However, current etiology, diagnosis and treatment remain unsatisfactory and no previous study has resolved this problem. Building on the strengths and limitations of previous cohort studies of MDD, the prospective cohort study of depression (PROUD) is a 3-year large-scale cohort study designed to collect multidimensional data with a flexible follow-up schedule and strategy. The goal is to establish a nationally representative, high-quality, standardized depression cohort to support precise diagnosis and treatment of MDD and address the gap in current research.

**Methods:**

PROUD is a patient-based, nationally representative multicenter prospective cohort study with baseline and 3-year follow-up assessments. It will be carried out from January 2022 to December 2026 in 52 qualified tertiary hospitals in China. A total of 14,000 patients diagnosed with MDD, according to the DSM-5 criteria, and aged ≥ 16 years, will be recruited to PROUD. Participants aged 18-65 years who have not received any treatment during a depressive episode will be included in the precision medicine cohort (PMC) of PROUD (*n*=4,000). Patients who meet the general eligibility criteria but not the PMC criteria will be included in the naturalistic observation cohort (NOC) of PROUD (*n*=10,000). A multiple follow-up strategy, including scheduled, remote, telephone, external visits and patient self-reports, will be implemented to collect comprehensive sociodemographic, clinical information, biospecimens, neuroimaging, cognitive function and electrophysiology data and digital phenotypes according to strict standard operating procedures implemented across centers. Trial registration: ChiCTR2200059053, registered on 23 April 2022, http://www.chictr.org.cn/showproj.aspx?proj=165790.

**Conclusions:**

PROUD is a prospective cohort study of MDD patients in China. It will provide a comprehensive database facilitating further analyses and aiding the development of homeostatic and precision medicine in China.

## Introduction

Homeostasis refers to a state in which the organism maintains the relative stability of the internal environment by regulating the coordinated activities of organs and systems. Homeostasis is the basis for maintaining health and ensuring various physiological functions. Conversely, the occurrence and development of disease is usually accompanied by an imbalance in the body's homeostasis (Qin and Wang, 2022). Major depressive disorder (MDD) is a highly prevalent and debilitating mental disorder with a lifetime prevalence among Chinese adults of 6.9% (Lu *et al.*, 2021). MDD has been identified as one of the leading contributors to global disease burdens (Diseases and Collaborators, 2020). However, its etiology is not yet fully understood, and despite being the focus of more attention in recent years, diagnosis and treatment remain unsatisfactory. Firstly, there are many possible causal factors for MDD, ranging from biological to psychosocial. It is generally believed to be the result of a combination of factors triggering an imbalance in homeostasis throughout the central nervous system. However, most previous studies have explored the pathogenesis of depression from a single dimension without considering the combined effect of multidimensional factors. Secondly, the clinical manifestation varies greatly among individuals and patient groups are highly heterogeneous. MDD remains difficult to diagnose with accuracy in clinical practice and Mitchell *et al*. found that only about 50% of true cases had been diagnosed (Mitchell *et al.,*
2009). Objective indicators of MDD have not been identified and professionals rely primarily on phenomenological descriptions for diagnoses (McCarron *et al.*, 2021; Su and Si, 2022). Finally, the effectiveness of treatment requires improvement. The overall cumulative remission rate was only 67% in the STAR*D study (Rush *et al.,*
2006) and rates of recurrence remain high at 77.1% over the 6-year follow-up (Verduijn *et al*., 2017), partly because objective evaluations of long-term efficacy are lacking and treatments are often based on practical experience (McCarron *et al.,*
2021; Su and Si, 2022). Owing to MDD heterogeneity and various other features, no previous study has resolved these problems (Cai *et al.*, 2020; Pine, 2019) and a novel, nationally representative cohort study may be of assistance. Therefore, the Prospective Cohort Study of Depression in China (PROUD) has been designed with careful consideration of MDD features. The PROUD study will (1) collect multidimensional data; (2) undertake large-scale recruitment of patients with different features from 24 provinces and cities; (3) collect data on clinical manifestation using a standardized procedure and (4) observe and describe the course of MDD over long-term follow-up.

Prospective cohort studies focusing on depression have been conducted in other countries and we have learned from their strengths and limitations while designing the PROUD study. The Netherlands Study of Depression and Anxiety (NESDA) and the Texas Resilience against Depression (T-RAD) study are two such studies. NESDA is an ongoing longitudinal naturalistic cohort study, investigating the course and consequences of depressive and anxiety disorders. Its design integrated biological and psychosocial perspectives within an epidemiological framework (Penninx *et al*., 2021; Penninx *et al.,*
2008). T-RAD includes two 10-year natural history prospective studies and aims to uncover multimodal factors predictive of onset and progression of depressive disorder, treatment responsivity and to identify subgroups of depression and facilitate precise diagnosis and effective intervention (Trivedi *et al.,*
2020). Major strengths of both studies include long-term follow-up and the collection of comprehensive multidimensional data. However, both studies have the limitations of a comparatively small sample size (3,328 for the NESDA study reported in 2021 and 2,500 for each study of the T-RAD) and fixed follow-up schedules which make timely capture of unexpected critical events leading to mood changes in patients difficult (Penninx *et al.*, 2021; Trivedi *et al.*, 2020). The PROUD study is designed as a 3-year cohort study collecting multidimensional data, biospecimens, neuroimaging and electroencephalogram (EEG) data, but with a larger sample of 14,000 patients and more flexible follow-up schedule and strategy, including external visits prompted by qualifying events.

There have been previous cohort studies of depression in China but the PROUD study has a larger scale and improved shareability of cohort data. The PROUD study aims to establish a nationally representative, high-quality, standardized depression cohort and to construct a comprehensive database for facilitation of further analyses and studies. It is hoped to promote the understanding of homeostatic medicine for MDD and facilitate the development of precise diagnoses and treatments, thus filling gaps in current research.

## Methods and Analysis

### Study design and settings

PROUD is a patient-based, nationally representative multicenter prospective cohort study with baseline and 3-year follow-up assessments. It will be carried out from January 2022 to December 2026 in 52 qualified tertiary hospitals in China, covering 24 provinces and cities: Beijing, Shanghai, Sichuan, Hunan, Hebei, Tianjin, Shandong, Guangdong, Yunnan, Zhejiang, Anhui, Jiangxi, Henan, Shenzhen, Shanxi, Fujian, Hubei, Jiangsu, Liaoning, Heilongjiang, Chongqing, Shaanxi, the Xinjiang Uygur Autonomous Region and the Inner Mongolia Autonomous Region, which are belong to five economic regions in China (Ma, 2009). Multidimensional data, including sociodemographic characteristics, clinical information, biospecimen, neuroimaging, cognitive function, electrophysiology and digital phenotypes, will be collected using standardized operating procedures and uniform equipment to guarantee quality across centers. Ethical approval was obtained from Beijing Anding Hospital, Capital Medical University, Beijing, China. The protocol has been registered in the Chinese Clinical Trial Registry platform (number: ChiCTR2200059053).

### Participants and eligibility criteria

The study population comprises MDD patients with diverse sociodemographic characteristics, disease stages and treatment regimens. About 14,000 eligible MDD patients will be recruited from 52 centers. MDD patients who have not received any treatment during the acute phase of the depressive episode will be included in the precision medicine cohort (PMC) of PROUD (*n*=4,000). Patients who meet the general eligibility criteria, but not the PMC criteria, will be included in the naturalistic observation cohort (NOC) of PROUD (*n*=10,000). There are no restrictions of the treatments and antidepressant agents for NOC cohort of PROUD. An additional 1,000 participants with no psychiatric history will be included as healthy controls (HC) and 1,000 participants with bipolar disorder will be included as diseased controls. The general flow chart of participant selection and evaluation can be found in Fig. 1.

**Fig. 1 Fig1:**
[figure not shown]
Flow chart of participant selection

### General inclusion criteria for PROUD

Males and females aged ≥16 years.Inpatients or outpatients with a diagnosis of major depressive disorder based on the Diagnostic and Statistical Manual of Mental Disorders, 5th Edition (DSM-5).Primary school education or above, able to understand the content of the scale.Participation on a voluntary basis and provision of written informed consent.

### General exclusion criteria for PROUD

Comorbidities of clinically diagnosed schizophrenia, bipolar disorder, neurodevelopmental disorders, neurocognitive disorders or other major psychiatric diseases.Severe medical conditions precluding participation in the study.Any other conditions considered unsuitable for the study.

### Additional inclusion criteria for PROUD-PMC

Males and females aged 18-65 years.A score of ≥14 on the 17-item Hamilton Depression Rating Scale (HAMD-17) at both screening and baseline.Have not taken any antidepressant agents for at least 14 d before screening (fluoxetine therapy should be discontinued at least 28 d before screening).Monotherapy for antidepressants planned.

### Additional exclusion criteria for PROUD-PMC

Depressive episodes secondary to a systemic disease or neurological disorder, such as depression due to hypothyroidism.Received modified electric convulsive therapy (MECT), transcranial magnetic stimulation (TMS), deep brain stimulation (DBS) or vagus nerve stimulation (VNS) within 3 months before screening.Withdrawal of psychotropic drugs did not equate to seven half-life periods before the screening.Women with a positive blood human chorionic gonadotropin (HCG)/urine HCG test; men with reproductive potential and women of reproductive age unable to use contraception effectively and women who plan to become pregnant within 3 months of the start of the study.Participated in any interventional clinical trial 3 months before screening.

### Data collection

An overview of data collection and assessments for field visits is shown in Table 1.

**Table 1 Tab1:** Overview of assessments during field visits

Category	Components	Field visits									
		Baseline	2 w^a^	8 w^a^	12 w^a^	24 w^a^	52 w	76 w^a^	104 w	128 w^a^	156 w
**Sociodemographic, Lifestyle**											
Sociodemographic characteristics	Sex, age, ethnicity, weight, height, education, occupation	**×**									
lifestyle and diet habits	Defecation, smoking, drinking, dietary habits, water intake, use of antibiotics and probiotics	**×**	**×**	**×**	**×**	**×**	**×**	**×**	**×**	**×**	**×**
**Clinical**											
History of present illness	Date of the first onset, date of the current illness onset, total number of episodes, family histories	**×**									
Physical examination	Blood pressure, pulse, temperature, respiration and other abnormal results	**×**	**×**	**×**	**×**	**×**	**×**	**×**	**×**	**×**	**×**
Comorbidities	Diagnoses, onset time, remission time, treatments	**×**	**×**	**×**	**×**	**×**	**×**	**×**	**×**	**×**	**×**
Treatment	Physical therapy, psychotherapy, psychiatric medications	**×**	**×**	**×**	**×**	**×**	**×**	**×**	**×**	**×**	**×**
Adverse events	Adverse events, concomitant medications		**×**	**×**	**×**	**×**	**×**	**×**	**×**	**×**	**×**
**Symptoms evaluation**											
HAMD-17	Hamilton Depression Rating Scale for Depression -17-item (observer-rated)	**×**	**×**	**×**	**×**	**×**	**×**	**×**	**×**	**×**	**×**
HAMA	Hamilton Anxiety Scale (observer-rated)	**×**	**×**	**×**	**×**	**×**	**×**	**×**	**×**	**×**	**×**
BPRS-4	Brief Psychiatric Rating Scale, BPRS 4-items (observer-rated)	**×**	**×**	**×**	**×**	**×**	**×**	**×**	**×**	**×**	**×**
C-SSRS	Columbia-Suicide Severity Rating Scale (observer-rated)	**×**		**×**	**×**	**×**	**×**	**×**	**×**	**×**	**×**
QIDS-SR16	Quick Inventory of Depressive Symptomatology-Self-Report (self-rated)	**×**	**×**	**×**	**×**	**×**	**×**	**×**	**×**	**×**	**×**
SHAPS	Snaith-Hamilton Pleasure Scale (self-rated)	**×**	**×**	**×**	**×**	**×**	**×**	**×**	**×**	**×**	**×**
GAD-7	Generalized Anxiety Disorder (self-rated)	**×**	**×**	**×**	**×**	**×**	**×**	**×**	**×**	**×**	**×**
PDQ-D5	Perceived Deficit Questionnaire for Depression 5-item (self-rated)	**×**	**×**	**×**	**×**	**×**	**×**	**×**	**×**	**×**	**×**
HCL-33	Hypomania Check List (self-rated)	**×**	**×**	**×**	**×**	**×**	**×**	**×**	**×**	**×**	**×**
FISER/GRSEB	Frequency and Intensity of Side Effects Rating/Global Rating of Side Effects Burden (self-rated)		**×**	**×**	**×**	**×**	**×**	**×**	**×**	**×**	**×**
PRISE	Patient Rated Inventory of Side Effects (self-rated)		**×**	**×**	**×**	**×**	**×**	**×**	**×**	**×**	**×**
PAQ	Patient Adherence Questionnaire (self-rated)		**×**	**×**	**×**	**×**	**×**	**×**	**×**	**×**	**×**
SDS	Sheehan Disability Scale (self-rated)	**×**		**×**	**×**	**×**	**×**	**×**	**×**	**×**	**×**
MIDAS	Migmine Disability Assessment Questionnaire (self-rated)	**×**			**×**		**×**		**×**		**×**
HIT-6	Headache Impact Test-6 (self-rated)	**×**			**×**		**×**		**×**		**×**
MAES	Modified Apathy Estimate Scale (observer-rated)	**×**					**×**		**×**		**×**
CFS-11	Chalder Fatigue Scale-11 (self-rated)	**×**					**×**		**×**		**×**
PSS	Perceived Stress Scale (self-rated)	**×**					**×**		**×**		**×**
CTQ	Childhood Trauma Questionnaire (self-rated)	**×**									
EPQ	Eysenck Personality Questionnaire (self-rated)	**×**									
BPX	Bipolarity index (observer-rated)	**×**									
Cognitive evaluation	The Chinese Brief Cognitive Test (C-BCT)	**×**		**×**			**×**		**×**		**×**

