#### Sociodemographic information and lifestyle habits

Sociodemographic information will be collected through a structured self-report questionnaire at baseline, including birth date, gender, height, weight, marital status, education level, occupational status, household income, living area, left-behind children experience and experience of being an only child. Also, data on lifestyle and dietary habits such as defecation, smoking, drinking, dietary habits, water intake and the use of antibiotics and probiotics will be collected. Information will also be collected about the history of the present illness, physical examination results, comorbidities, treatments and adverse events.

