#### Secondary outcomes

Hospitalization for psychiatric episodes or emotional events.Conversion to bipolar disorder: DSM-5-diagnosed manic or hypomanic episodes.High risk of suicide: score on the third item of the HAMD-17 ≥3 or answering “Yes” to item 4 or 5 of the C-SSRS.Adverse effects of drug treatment and cumulative drug exposure.Adherence to treatment, as measured with the PAQ. Not taking prescribed drugs ≥70% of the time is considered to indicate non-adherence.Changes in social functions in the acute, consolidation and maintenance phases compared with those at enrollment.Changes in cognitive function in the acute, consolidation and maintenances phase compared with those at enrollment.Changes in multi-omics, neuroimaging, electrophysiology and digital phenotype indicators.

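### Table 1 has no baseline rating on the side-effect scales and no follow-up weight, so neither gives a change from baseline, and complaints present at entry may be misattributed to drug treatment

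*Protocol article*

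**What the plan says.** All schedule statements are from Table 1 of the Protocol article unless another section is named.

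- **Side-effect scales.** The rows for PRISE ("Patient Rated Inventory of Side Effects (self-rated") and FISER/GRSEB ("Frequency and Intensity of Side Effects Rating/Global Rating of Side Effects Burden (self-rated") have an empty baseline cell and a mark at every later visit. The adherence questionnaire (PAQ) and the row "Adverse events, concomitant medications" follow the same pattern.
- **Weight.** It appears in the sociodemographic row, "Sex, age, ethnicity, weight, height, education, occupation", which is marked at baseline only. The section on sociodemographic information and lifestyle habits gives the source: "Sociodemographic information will be collected through a structured self-report questionnaire at baseline". The physical examination is repeated at every visit, but its content is "Blood pressure, pulse, temperature, respiration and other abnormal results", which does not name weight.
- **Outcome.** Secondary outcomes include "Adverse effects of drug treatment and cumulative drug exposure". The Data analysis section plans prediction models for primary and secondary outcomes.
- **Treatment at entry.** For the naturalistic cohort: "There are no restrictions of the treatments and antidepressant agents for NOC cohort of PROUD". The additional PMC criteria, by contrast, require a drug-free interval before screening.

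**The concern.** Insomnia, fatigue and gut complaints can belong to depression or to its treatment. A side-effect checklist first completed two weeks into treatment records that a complaint is present, but not whether it was there before the first dose. PMC patients enter with a HAMD-17 score of at least 14, so pre-existing complaints are to be expected.

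In NOC the difficulty is different. Some patients may already have side effects from existing treatment when they enrol. If the first rating on these scales comes a year later, a side effect carried in at entry looks the same as one that arose during follow-up.

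What is at stake is the meaning of the adverse-effect outcome and of any model that predicts it. A baseline rating that was never taken cannot be recovered by a later analysis plan.

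Weight is a separate matter. There is a baseline value but no scheduled later one, so weight change under treatment cannot be described from the schedule shown.

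**Working it through.** The document has no sample-size or power figure tied to this point, so the check is a count of scheduled ratings in Table 1.

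**Visits.** Table 1 has ten field visits: baseline and weeks 2, 8, 12, 24, 52, 76, 104, 128 and 156, so 10 − 1 = 9 are after baseline. Its footnote reserves six of these (2, 8, 12, 24, 76, 128) for PMC, which leaves NOC 9 − 6 = 3 (52, 104, 156).

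| Item | Baseline | Follow-up, PMC | Follow-up, NOC | Same-measure change possible? |
|---|---|---|---|---|
| PRISE | 0 | 9 | 3 | No |
| FISER/GRSEB | 0 | 9 | 3 | No |
| PAQ | 0 | 9 | 3 | No |
| Weight | 1 | 0 | 0 | No |
| HAMD-17, for comparison | 1 | 9 | 3 | Yes |

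The section on additional PMC follow-up names only weeks 2, 8 and 12 as extra field visits. On that reading the PMC count is 3 + 3 = 6 rather than 9. The zeros at baseline do not change.

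**Share in NOC.** 10,000 / 14,000 = 71.4%. This is a ceiling for the concern about treatment at entry. The document does not say how many NOC patients will be on drugs when they enrol, and a patient can fall into NOC for other reasons, such as age or a HAMD-17 score below 14.

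**Does the text supply the missing rating?** The Clinical assessment section lists PRISE and FISER/GRSEB among self-report measures, after a sentence on scales used at baseline. That list has no timing of its own. It also contains the Remote Follow-Up Checklist, a follow-up tool, so it does not override the empty cells in Table 1.

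**What else could stand in?** Baseline data include HAMD-17, HAMA, QIDS-SR16, GAD-7, a fatigue scale (CFS-11), a headache scale (HIT-6), defecation, comorbidities and sleep from wearable devices. These are different instruments, and some are not repeated early: HIT-6 next appears at week 12 and CFS-11 at week 52. Telephone visits every three months cover treatment, medication use and outcomes, and patients may report adverse events themselves. Neither route is said to carry PRISE, FISER/GRSEB or weight.

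**The case against.** The strongest case on the other side has five parts.

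1. **No stated outcome is contradicted.** Social and cognitive function are defined as changes from enrolment; adverse effects are not, and weight change is not a named outcome. This stands. The point is a design weakness, not an inconsistency.
2. **No counting rule is stated.** A reader might infer that every item endorsed on PRISE will be counted as a drug effect. The document does not say so. It ties no scale to the outcome, it keeps a separate adverse-event record, and attribution rules may sit in the full protocol or SAP. Misattribution is therefore a risk, not a stated consequence.
3. **PMC patients are off drugs at entry.** The PMC criteria require a drug-free interval, so a burden or adherence rating at baseline would have little to measure. This stands for FISER/GRSEB and PAQ. It does not remove the value of a baseline symptom checklist such as PRISE, because the question in PMC is what was present before treatment.
4. **Other data fill the gap.** They do so in part: severity, fatigue, headache and bowel habit can be adjusted for, and telephone visits shorten the year-long interval in NOC. None is a rating on the same scale, and NOC side effects at entry have no dedicated scale.
5. **Table 1 is an overview in a condensed article.** Some items, such as marital status and certain imaging sequences, appear only in the text, and the physical examination row ends with an open phrase. This weakens the weight point, since the full protocol may schedule it. It weakens the side-effect point less: empty baseline cells beside filled ones are a stated schedule.

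**Conclusion.** The point holds as a limited, cheaply corrected weakness. As scheduled, the side-effect scales have no baseline rating in either cohort and weight has no follow-up value, so neither gives a same-measure change. Complaints present before treatment in PMC, or under existing treatment in NOC, may be misattributed in the adverse-effect outcome and in models of it. The concern about side effects carried in from existing treatment applies mainly to NOC. The weight gap stands on its own and does not lead to symptoms being counted as side effects.

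The schedule applies to all 14,000 patients, but that is not the number misclassified. That number would depend on how common each complaint is before treatment, how often it persists and how it is attributed, and the document gives none of these. A reader might also infer that models of adverse effects would do little more than recover baseline severity. Nothing in the document supports that, and baseline severity is measured and can be entered in the models.

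The verdict assumes that Table 1 reflects the working schedule of field visits.

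**What to change.** In Table 1:

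- mark PRISE at baseline for all patients, completed before treatment starts in PMC;
- mark FISER/GRSEB and PAQ at baseline for NOC patients already on treatment;
- add measured weight to the physical examination row, so that it is taken at each field visit including baseline.

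Analyse side-effect complaints as new or worse than baseline. For NOC patients already treated, the baseline rating separates complaints present at entry from later ones; it does not separate drug effects from depression, and reports should say so. Report patients enrolled before the change separately, because they will lack the baseline ratings.

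The cost is a few minutes of extra self-rating at baseline and a scale reading at visits that already include a physical examination. No visit is added. If the full protocol already schedules any of these items, it is enough to bring Table 1 into line with it.
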